#### Outcome measures

We will assess healthcare utilization across four types of care settings, including ED, primary care, substance use treatment center, and mental health service facility (Fig. 1).ED visits will be identified in APCD using HCPCS (99,281–99,285) and revenue codes (0450–0459, 0981). Uninsured ED visits will be identified in SEDD using OUD and MOUD diagnosis codes. Given the lack of unique identifiers in SEDD, each record represents a single encounter.Primary care visits will be identified using CPT codes for outpatient visits (9201–99215, 99,381–99,397), HCPCS code T1015, and provider specialty codes (01, 08, 11, 19, 31, 38, 50, 84, 97) indicating primary care (e.g., internal medicine, family medicine, nurse practitioners, physician assistants).Substance use treatment visits will be identified via CPT codes for substance use services (e.g., H0015, H0018, H0020), including MOUD-related services. Claims will be restricted to facilities verified as SAMHSA-regulated Opioid Treatment Programs (OTPs) in Rhode Island. We recognize that office-based MOUD services are increasingly provided in primary care and other outpatient settings; however, these visits will be captured under the primary care setting definition.Mental health service visits will be identified using CPT codes (90,791–90853, 99,404) and provider taxonomy for psychiatry, psychology, and behavioral health providers.

**Fig. 1 Fig1:**
[figure not shown]
Overview of three aims in our study

In particular, we will assess receipt of HIV prevention services, including HIV testing and PrEP, as well as MOUD. We will use CPT codes (86,689, 86,701–86703, 87,534–87,536, 87,390) and HCPCS codes (G0432–G0435) to identify claims for HIV testing. PrEP use will be defined as having a prescription for a 30-day or longer supply of tenofovir/emtricitabine or tenofovir alafenamide/emtricitabine, without a concurrent diagnosis of HIV or hepatitis B virus. MOUD receipt will use the definitions stated above, based on NDC and procedure codes. All utilization outcomes will be summarized and stratified by care setting and insurance type where applicable. We will also explore temporal trends across the study period.

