#### Data sources

We will use two primary data sources to capture insured and uninsured individuals in RI:Rhode Island (RI) All-Payer Claims Database (APCD) includes longitudinal medical and pharmacy claims, participant demographics and enrollment information, and provider characteristics data from private insurers, Medicare, and Medicaid (Table 1). APCD data are updated monthly and reflect over 90% of the insured population in RI (based on our preliminary analysis). We will use APCD data between 2012 and 2022 to evaluate trends over time.Rhode Island State Emergency Department Database (SEDD): Captures encounter-level data for ED visits, including those involving uninsured individuals (estimated 5.0% of RI population, based on 2022 data) [48]. While SEDD lacks unique patient identifiers and pharmacy/provider details, it complements APCD by providing a more complete picture of ED utilization among patients who may be excluded from claims-based analyses. Because SEDD does not allow for longitudinal tracking of individuals across visits, these data will be used to characterize encounter-level trends among the uninsured population. APCD and SEDD will not be linked at the individual level; however, each will be analyzed separately but interpreted together to capture utilization across the full population of people with OUD.

**Table 1 Tab1:** Data variables for statistical analysis in Aim 1

Demographic data	Medical care information	Provider information
Age Sex ZIP Code City Insurance information Relationship to health policyholder Internal unique identifier	Date of service Type of service Location of service Date prescription(s) filled ICD-9/10 diagnostic codes National Drug Code Prescription refill indicator Pharmacy ID Inpatient and outpatient claims Mental health claims	Practice Attending provider name Prescribing provider name Type Primary care indicator Specialty Address ZIP Code City Pharmacy ID

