**Fig. 2 Fig2:**
[figure not shown]
Flowchart of retrospective data analysis in Aim 1

In descriptive analysis, we will summarize annual frequencies and rates of healthcare utilization and HIV prevention service uptake by setting and insurance status. Results will be stratified by age group, gender, race/ethnicity, and geographic region. Statistical tests (e.g., Chi-square, t-test, and ANOVA) and trend analyses will be used to examine differences in service utilization across years and subgroups.

In regression modeling, we will fit multivariable logistic regression models to identify individual- and area-level factors that are associated with receipt of HIV testing, PrEP uptake and retention, and MOUD initiation and retention (defined as continuous MOUD coverage for 180 days, permitting gaps no longer than 7 days) [49]. Covariates will include demographic characteristics (age, gender, race/ethnicity), insurance type, healthcare setting, and SDH indicators (e.g., housing instability, incarceration). Area-level variables from the U.S. Census Bureau (i.e., American Community Survey) will be linked to each individual via zip codes. If data structure allows, we will implement multilevel models to account for clustering at the geographic level. We will report adjusted odds ratios (aORs) with 95% confidence intervals. We will conduct several sensitivity analyses with alternate definitions of PrEP use and retention (e.g., 60-days of supply, and allowing for various lengths of gaps between refills). All analyses will be conducted using SAS 9.4. Statistical significance will be assessed at the *p* < 0.05 level unless otherwise specified.

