#### Outcome definition

The base model will represent the status quo—current levels of HIV prevention service delivery across different care settings, as established through Aim 1. Using Python™, we will evaluate the effect of each proposed implementation strategy (developed in Aim 2) on multiple outcome measures over 5- and 10-year projections.

Key outcomes will include projected HIV incidence across the population, as well as the number of new HIV cases averted or caused relative to the base model. We will also assess changes in healthcare utilization patterns and quantify uptake of PrEP and MOUD by setting. For each intervention scenario, we will calculate the number needed to treat (NNT)—defined as the number of HIV prevention service encounters or MOUD prescriptions required to prevent a single HIV infection over a specified time horizon. And lastly, the model will assess the population-level impact of integrating HIV prevention services into OUD care. These outcomes will guide the selection of the most effective and feasible strategy package for real-world implementation and inform the prioritization of approaches for future pilot testing and scale-up.

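### The primary PrEP definition has no rule to set aside post-exposure prophylaxis recorded at 30 or more days, although the claims could support one; the size of the error is unknown and may be nil

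*Protocol article*

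**What the plan says.** The protocol article fixes the PrEP outcome in Aim 1, Outcome measures: "PrEP use will be defined as having a prescription for a 30-day or longer supply of tenofovir/emtricitabine or tenofovir alafenamide/emtricitabine". The only exclusions are two diagnoses; the person must be "without a concurrent diagnosis of HIV or hepatitis B virus". Post-exposure prophylaxis is not mentioned anywhere in the article, and the rule does not look at other antiretrovirals filled around the same date.

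The same section adds: "All utilization outcomes will be summarized and stratified by care setting and insurance type where applicable". The Analysis plan makes PrEP uptake and retention outcomes of the logistic models. It also plans sensitivity analyses using "alternate definitions of PrEP use and retention (e.g., 60-days of supply, and allowing for various lengths of gaps between refills".

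On data, the Data sources section says that the APCD "includes longitudinal medical and pharmacy claims, participant demographics and enrollment information, and provider characteristics data"; Table 1 lists diagnosis codes, National Drug Codes (NDCs), fill dates and a refill indicator. The emergency department database (SEDD) differs: "While SEDD lacks unique patient identifiers and pharmacy/provider details".

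In Aim 3, Outcome definition, the base model is set to "current levels of HIV prevention service delivery across different care settings, as established through Aim 1". Table 2 gives time on PrEP as an example parameter.

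**The concern.** The definition identifies a drug product and a length of supply, not the purpose of the prescription. Suppose a person without HIV or hepatitis B is given post-exposure prophylaxis that includes the same two-drug combination, and the claim records 30 days or more. That person meets every element and enters the numerator as a PrEP user.

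Two errors follow from one such record. Uptake is counted where there was none. If the course is a single fill, it would probably also appear as a PrEP user who stopped early, so uptake is pushed up and apparent persistence down. Because PrEP is rare, a small absolute number of these records can be a noticeable fraction of the counted users. The estimates feed the regression outcomes and, through the status quo scenario, the starting point of the agent-based model.

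**Working it through.** The plan states no figure that can be reproduced: there is no post-exposure rate, course length or dispensed quantity, and no rule that ties a pharmacy fill to a care setting. The check is therefore a reading of the rule followed by an illustration.

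**Which records pass the rule**

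- Post-exposure course recorded with fewer than 30 days: fails the days-of-supply test and is not counted.
- Post-exposure course recorded with 30 or more days, no HIV or hepatitis B diagnosis: counted as PrEP.
- The same course with another antiretroviral filled on the same day: still counted, because other antiretrovirals are not examined.
- SEDD records: not affected, because there are no pharmacy data from which PrEP could be counted.

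**What the 60-day analysis does**

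A single 30-day post-exposure fill drops out. So does a true PrEP user who stopped after one 30-day fill. A true user with one fill of 60 days or more stays in. If the estimate falls between the 30-day and 60-day versions, the fall mixes post-exposure courses with early stopping and cannot be assigned to either. The comparison does give an upper bound on the effect of single 30-day post-exposure fills, but the primary estimate does not change.

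**Illustration of size**

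Inputs:

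- p, the true PrEP rate: 1.2% and 2.2%, borrowed from the article's background section on barriers, where they are cited rates of PrEP initiation following emergency department visits. They are not estimates for this cohort.
- q, the rate of post-exposure fills in the same group: assumed at 0.1%, 0.5% and 1.0%.
- f, the share of those fills recorded with at least 30 days: assumed at 0, 0.5 and 1.

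False share of counted PrEP = q·f / (p + q·f).

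| q | f = 0 | f = 0.5 (p = 2.2% to 1.2%) | f = 1 (p = 2.2% to 1.2%) |
|---|---|---|---|
| 0.1% | 0% | 2.2% to 4.0% | 4.3% to 7.7% |
| 0.5% | 0% | 10.2% to 17.2% | 18.5% to 29.4% |
| 1.0% | 0% | 18.5% to 29.4% | 31.2% to 45.5% |

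Worked example: q = 0.5%, f = 1, p = 1.2% gives 0.5 / (1.2 + 0.5) = 0.5 / 1.7 = 29.4%.

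**Effect on the gap between eligibility and uptake**

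The same background section says that one-third of emergency department patients qualified for PrEP. With no error the gap is 33.3 − 2.2 = 31.1 to 33.3 − 1.2 = 32.1 points. Adding the largest assumed error, 1 point, gives 30.1 to 31.1 points. The gap shrinks by about 3% (1/32.1 to 1/31.1). The distortion is potentially large relative to counted PrEP and small relative to unmet need.

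**The case against.** The strongest reply is that the mechanism depends on facts outside the article. The article does not say that post-exposure courses use this combination with another drug, nor that they are recorded at 30 days. The 30-day floor already removes shorter records, and the bias may be zero. That stands, and it limits the point to a gap in the rule, not a demonstrated bias.

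A reader might infer that the error is worst in the emergency department. The documents do not support this: they give no post-exposure frequency by setting and no rule attributing fills to settings, stratification is promised only where applicable, and uninsured emergency visits carry no pharmacy data.

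A reader might also infer that the error would hide the prevention gap. The arithmetic above shows that it would not. Nor can one say that every such course would score as not retained, because the article gives no PrEP retention rule; its 180-day definition is for medications for opioid use disorder.

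On the model, inputs also come from literature and Aim 2, the model is calibrated to observed HIV incidence, and each parameter is varied in one-way sensitivity analyses. No change in the ranking of strategies has been shown.

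Finally, detailed drug-code lists are commonly left to a fuller document. That does not dispose of the point, because the article states the PrEP rule with its exclusions, and Table S1 is described as listing codes for cohort identification. The 60-day and refill-gap variants are offered only as examples, so a further variant could be added, but a sensitivity analysis alone would leave the primary definition as it is.

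**Conclusion.** The point holds in a limited form. As stated, the primary definition would count as PrEP any post-exposure course recorded with 30 or more days of the two-drug combination in a person without a concurrent HIV or hepatitis B diagnosis, and the planned 60-day analysis cannot separate such courses from early discontinuation. This assumes that some post-exposure courses use the combination and are recorded at that length, which the documents neither state nor exclude.

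The size cannot be determined from the documents. It is nil if all such courses are recorded below 30 days, and reaches 31% to 45% of counted PrEP only at the most adverse assumptions tried. Its spread across settings is unknown, and it is confined to APCD data. This is a cheap improvement to a primary outcome definition, not evidence that the Aim 1 results or the model conclusions would be wrong.

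**What to change.** Add to the PrEP definition in Aim 1, Outcome measures, that a two-drug fill is not counted as PrEP when another antiretroviral is filled at about the same time, for example within 7 days either side. The 7 days is a working choice with no source in the documents, so vary it. The NDCs and fill dates in Table 1 are sufficient to build the rule.

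Tabulate the excluded fills, so that the size of the problem is seen. Label them as two-drug fills accompanied by another antiretroviral, not as confirmed post-exposure prophylaxis, since claims alone do not establish the indication.

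Exclude single fills that carry an HIV-exposure diagnosis only as an added sensitivity analysis. In the primary definition that exclusion would also remove true PrEP starters who filled once.

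Cost: one more NDC list and one date rule in the SAS code. Some people who move directly from post-exposure prophylaxis to PrEP will enter one fill late. A course whose companion drug leaves no pharmacy claim would still be counted.

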#### Covariates

Where feasible, we will link individual claims to neighborhood-level characteristics using residential ZIP codes or census tracts. Data from the American Community Survey (ACS) and other Census Bureau resources will be used to assign area-level indicators of socioeconomic status, including median household income, educational attainment, and housing instability. We will also examine area-level incarceration rates and opioid-related mortality where available. These variables will be used descriptively and incorporated into regression models as contextual covariates. Examples of data variables to be used in our analysis are summarized in Table 1.

#### Analysis plan

Statistical analyses include descriptive analysis and regression modeling (Fig. 2).

**Fig. 2 Fig2:**
[figure not shown]
Flowchart of retrospective data analysis in Aim 1

In descriptive analysis, we will summarize annual frequencies and rates of healthcare utilization and HIV prevention service uptake by setting and insurance status. Results will be stratified by age group, gender, race/ethnicity, and geographic region. Statistical tests (e.g., Chi-square, t-test, and ANOVA) and trend analyses will be used to examine differences in service utilization across years and subgroups.

In regression modeling, we will fit multivariable logistic regression models to identify individual- and area-level factors that are associated with receipt of HIV testing, PrEP uptake and retention, and MOUD initiation and retention (defined as continuous MOUD coverage for 180 days, permitting gaps no longer than 7 days) [49]. Covariates will include demographic characteristics (age, gender, race/ethnicity), insurance type, healthcare setting, and SDH indicators (e.g., housing instability, incarceration). Area-level variables from the U.S. Census Bureau (i.e., American Community Survey) will be linked to each individual via zip codes. If data structure allows, we will implement multilevel models to account for clustering at the geographic level. We will report adjusted odds ratios (aORs) with 95% confidence intervals. We will conduct several sensitivity analyses with alternate definitions of PrEP use and retention (e.g., 60-days of supply, and allowing for various lengths of gaps between refills). All analyses will be conducted using SAS 9.4. Statistical significance will be assessed at the *p* < 0.05 level unless otherwise specified.

### Aim 2 – Strategy development via EBQI panels

#### Study design

The objective of Aim 2 is to collaboratively develop and refine implementation strategies for integrating HIV prevention services and MOUD into real-world healthcare settings serving people with OUD in RI. This aim builds upon the findings of Aim 1 and existing literature, and leverages a EBQI model, engaging a multidisciplinary workgroup of key stakeholders through a series of structured panels.

#### Stakeholder recruitment

We will recruit a diverse group of 30 stakeholders across three key groups: healthcare providers, policy leaders, and people with lived experience (PWLE) of OUD. Specifically, we plan to include 10 healthcare providers (e.g., physicians and nurses) from various specialties such as emergency medicine, primary care, mental health, addiction medicine, and HIV treatment. Another 10 members will be public health and policy-level decision-makers involved in OUD service delivery or health system planning, including leadership from state agencies, social services, and healthcare organizations. Finally, we will recruit 10 community advocates with lived experience (current or past) of OUD, and/or involvement in harm reduction services. Participants will be recruited through existing networks such as the Rhode Island Overdose Prevention & Intervention Task Force, nonprofit organizations, and the Brown University Health network. All stakeholders will be invited to participate in a series of five EBQI panel sessions. PWLE will contribute perspectives on barriers to accessing HIV prevention services, stigma, and preferences for service delivery. Provider and policymaker participants will focus on identifying regulatory, clinical, and logistical barriers and facilitators to implementation. All participants will provide informed consent, and ethical oversight will be maintained throughout. Each participant will be compensated $200 per session.

#### EBQI procedures

The five in-person EBQI sessions are designed to follow a logical sequence that begins with sharing findings from Aim 1 and culminates in a finalized strategy package to be tested in Aim 3. EBQI activities will be guided by existing implementation frameworks and methods. The Consolidated Framework for Implementation Research (CFIR) will inform structured discussions around multi-level barriers in the implementation of HIV prevention care [50, 51]. Prior to the first session, the research team will prepare a summary of Aim 1 findings and an updated literature review of existing implementation strategies that have been used for care integration. These materials will be reviewed and refined in collaboration with stakeholders during the EBQI process. Each EBQI session, facilitated by the research team, will last approximately two hours.

##### Session 1: Introduction and presentation of aim 1 findings

This session will establish a shared understanding of the project's goals and introduce participants to the findings from Aim 1 and literature review. The research team will start the session with an introduction of the workgroup (stakeholders and research team members), followed by a presentation of healthcare utilization patterns and service gaps. Stakeholders will provide feedback through a member-checking process, ensuring findings reflect real-world experience. The session will conclude with an initial discussion about promising care settings for integrating HIV prevention services, and their potential impacts.

##### Session 2: Identification of implementation strategies

Prior to Session 2, the research team will use the barriers identified through Aim 1 analysis and synthesis of Session 1 to identify a “menu” of promising implementation strategies using the CFIR-ERIC matching tool [52]. The primary purpose of Session 2 is to bring this “menu” of implementation strategies to stakeholders to identify the most impactful strategies and to generate novel strategies. Participants will be grouped by role to ensure equitable input from PWLE, healthcare providers, and policymakers. Each group will map strategies to care settings and present recommendations to the full panel for refinement.

##### Session 3: Refinement and operationalization

In Session 3, participants will further refine selected strategies (from Session 2) by discussing feasibility, scalability, and necessary resources. They will define key implementation components, including action, roles, delivery methods, required resources, and target outcomes [53]. The workgroup will develop timeline and processes for integration into current workflows, as well as key performance indicators (KPIs) to guide future implementation evaluation. Select KPIs—such as service uptake rates, frequency of care engagement, and provider adherence—will also inform the parameterization of the agent-based model (Aim 3), ensuring that simulation scenarios are grounded in stakeholder-defined expectations. Special emphasis will be placed on addressing the needs of uninsured populations and accounting for social determinants of health.

##### Session 4: Review of draft strategies

The research team will first present the refined strategies developed from Session 3. Stakeholders will review the strategies for alignment with project goals, practical relevance, and cultural competence, and identify outstanding implementation barriers and feasibility concerns. Feedback will be incorporated in real time to make final adjustments.

##### Session 5: Finalization of strategy package

In the final session, the research team will present finalized implementation strategies. The workgroup will rank these strategies on their importance and feasibility, and confirm consensus on the selected implementation strategies to be evaluated through agent-based modeling in Aim 3. If consensus cannot be reached, structured decision-making techniques (e.g., breakout discussions, ranked-choice voting) will be used. And lastly, the workgroup will discuss potential steps beyond the study, including considerations of real-world deployment, sustainability, and post-implementation evaluation. While actual implementation is not part of the current study, such discussion could inform potential operationalization in future research and inform local implementation efforts.

